## Table of changes:

| Change                                            | Rationale                                                                                                                                                                                                                                                                                                                                                                                                                                                                                                                                              | Affected protocol section                                                                         |
|---------------------------------------------------|--------------------------------------------------------------------------------------------------------------------------------------------------------------------------------------------------------------------------------------------------------------------------------------------------------------------------------------------------------------------------------------------------------------------------------------------------------------------------------------------------------------------------------------------------------|---------------------------------------------------------------------------------------------------|
| Timepoints of data collection                     | Seroprevalence is assessed in month 0, 2, 4, 6, 8, 10, instead of week 0, 8, 16, 24, 32 and 40 since data collection within one week was not practically feasible. Bimonthly sample collection of all 69 NHs currently occurs in $\pm$ 4 weeks instead of $\pm$ 21 days. In each NH, the 2nd, 3rd, 4th, 5th and 6th sample collection are conducted respectively 60, 120, 180, 240 and 300 days after the first sample collection took place in the NH with a margin of $\pm$ 7 days instead of $\pm$ 4 days.                                          | 2.1 Objectives
2.4 Study design and population
3. Data analysis
4.3 Bias and limitations |
| Secondary objectives                              | This study was designed late 2020, when COVID-19 vaccines were still in research development. However, on January 5 th , 2021, the vaccination campaign in Belgian NH started. The implementation of vaccines directly impacts the seroprevalence, meaning that some of the secondary objectives were no longer accurate (e.g., assessment of risk factors for infection). Therefore, adjustments were made to the secondary objectives, and tertiary objectives concerning the proportion in the sample that is not vaccinated were added. | 2.1 Objectives
3. Data analysis                                                                |
| Additional questions concerning vaccine hesitancy | In the first test round we observed that 15% of staff in the sample were not vaccinated against COVID-19. Therefore, we aim to explore the reason behind vaccine hesitancy by adding additional questions in the follow-up questionnaire of the following sampling point concerning if and why they hesitated/are hesitating to get vaccinated as a part of the follow-up questionnaire (one-off).                                                                                                                                                     | 2.7.2 Demographic and medical data
6.3 Appendix: questionnaires                                |
| Statistical analysis                              | The statistical analysis plan was adjusted to the changes made in the secondary objectives and addition of tertiary objectives.                                                                                                                                                                                                                                                                                                                                                                                                                        | 3. Data analysis                                                                                  |

# **1. Background and objectives**

Statistics on reverse-transcriptase polymerase chain reaction (RT-PCR)-confirmed SARS-CoV-2 cases and deaths aid in monitoring the dynamics of disease propagation. However, diagnostic RT-PCR testing is far from ideal when trying to estimate the proportion of the population infected, a key indicator for public health decision making in the ongoing COVID-19 pandemic (Roda et al., 2020). For example, mildly affected or asymptomatic individuals are often not screened. Furthermore, RT-PCR-based testing yields only an epidemiological snapshot, because it fails to detect persons that already cleared SARS-CoV-2, making it difficult to infer the true proportion of the population that has been infected. Also, during the first months of the pandemic, most countries, including Belgium, did not have an adequate RT-PCR testing capacity for screening of anyone suspected or at risk of infection with SARS-CoV-2. As a result, the number of confirmed SARS-CoV-2 infections is largely underestimated (Verity et al., 2020).

In this context, seroprevalence surveys are of utmost importance. These studies can assess the proportion of the population that has already developed SARS-CoV-2 antigen-specific antibodies () and might potentially be protected against subsequent infection (Lipsitch et al., 2020). As recommended by WHO, monitoring changes of seroprevalence over time is also crucial to anticipate the dynamics of the pandemic and plan an adequate public health response (WHO, 2020). So far, seroprevalence data are available in Belgium for the general population (4.3%; blood donors) (Rode Kruis, 2020), ITG (8.4) (MAY 2020) and hospital staff (6.4%) (Steensels et al., 2020). Additionally, a national study among health care workers in Belgian hospitals showed an anti-SARS-CoV-2 IgG seroprevalence of 7.7% (Mortgat et al., 2020). Few data are available concerning the SARS-CoV-2 seroprevalence among nursing home (NH) residents and staff in Belgium, although these populations suffered from severe local SARS-CoV-2 outbreaks. Elderly are at high risk to develop severe cases of COVID-19, as 27% of the

total of the 9878 COVID-19 fatal cases in Belgium (between March 8th and June 2nd 2020) were reported from nursing homes (Sciensano, 2020). In May 2020, a pilot baseline seroprevalence study was conducted in NHs among Flanders, which showed that 24,5% and 19,1% of respectively NH residents and staff developed SARS-CoV-2 antigen-specific antibodies. Among the nine different nursing homes included in this study, a large variation in seroprevalence was seen ranging from 0,0% to 38,4% and 5,2% to 31,0% for residents and staff respectively (*unpublished data*). However, the degree of seroprevalence and sero-incidence for NHs in Brussels and Wallonia remains unknown. Furthermore, the pilot study conducted in May 2020 assessed the seroprevalence 4 to 6 weeks after the peak incidence of the first epidemic wave. Additionally, when a COVID-19 vaccination will be implemented, it will be of crucial importance to monitor the seroprevalence in Belgian nursing homes and assess the degree of persistence of this vaccine-induced immune response.

Therefore, our major study goals are to assess the current seroprevalence of SARS-CoV-2 in NH residents and staff in Belgium with subsequent 2-monthly follow-up of the sero-incidence over a period of 10 months. Furthermore, many questions remain unsolved about the proportion of asymptomatic cases of SARS-CoV-2 antibody positive NH residents and staff (and about their individual risk factors). Our secondary study goal is to gain additional insights on the association between seropositivity, clinical manifestation and COVID-19 disease outcome.

## **2. Methods**

### **2.1 Objectives**

#### **Primary objectives**

1. Assess the seroprevalence of SARS-CoV-2 among NH residents and staff in Belgium at month 0 and at every follow-up visit in the cohort at month 2, 4, 6, 8 and 10..
2. Assess the sero-incidence of SARS-CoV-2 among NH residents and staff in Belgium over five two month time frames and summarised over a ten month time period.

#### **Secondary objectives**

1. To assess the seroprevalence according to vaccination status among NH residents and staff in Belgium at month 0 and at every follow-up visit in the cohort at month 2, 4, 6, 8 and 10.
2. To assess the risk of getting a SARS-CoV-2 infection since vaccination between:
  - Residents and staff
  - Seropositive and seronegative participants at all timepoints
  - Individuals with or without previous self-reported SARS-CoV-2 infections
  - Adjusted for the updated vaccination degree of NH at all timepoints
3. To assess the proportion of confirmed COVID-19 deaths and non-COVID-19 related deaths and the time until death since vaccination (within the study timeframe) between sero-positive and -negative participants for NH residents
4. To assess the duration of SARS-CoV-2 specific antibody responses (seroreversion/no antibody response) since vaccination among NH residents and staff in Belgium.

#### **Tertiary objectives**

1. To assess the risk of getting SARS-CoV-2 infected between vaccinated and non-vaccinated (at last visit) residents/staff.

2. To assess the proportion of confirmed COVID-19 deaths and non-COVID-19 related deaths and the time until death (within the study timeframe) between vaccinated and non-vaccinated residents.
3. To assess the duration of SARS-CoV-2 specific antibody responses (seroreversion/no antibody response) since self-reported infection in a non-vaccinated residents/staff.

## 2.2 Project planning

We plan the current proposal into four work packages (WPs) outlined below (Table 1). **WP1** will focus on obtaining ethical clearance. In **WP2** we will take a random sample of NHs, recruit the NHs willing to participate, and subsequently randomly sample all participants. In **WP3**, capillary blood samples and COVID-19 related medical data will be collected over a period of 10 months. Analysis and reporting will be performed in **WP4**. However, given the rapid changes of the epidemic evolution and dynamics, the foreseen timeline is subjected to re-evaluation. If necessary, the foreseen timeline for testing will be re-considered, depending on the epidemiological situation (see special considerations and circumstances).

**Table 1.** Timelines foreseen in current study proposal. WP, work package. Grey cells indicate months spent for the specific task.

|            |                                                                   | Nov 2020 | Dec 2020 | Jan 2021 | Feb 2021 | March 2021 | April 2021 | May 2021 | June 2021 | July 2021 | August 2021 | Sept 2021 | Oct 2021 | Nov 2021 | Dec 2021 | Jan 2022 | Feb 2022 | March 2022 |
|------------|-------------------------------------------------------------------|----------|----------|----------|----------|------------|------------|----------|-----------|-----------|-------------|-----------|----------|----------|----------|----------|----------|------------|
| WP1 | Ethics                                                            |          |          |          |          |            |            |          |           |           |             |           |          |          |          |          |          |            |
| WP2 | Stratified random sampling and recruiting NHs                     |          |          |          |          |            |            |          |           |           |             |           |          |          |          |          |          |            |
|            | Stratified random sampling and recruitment of staff and residents |          |          |          |          |            |            |          |           |           |             |           |          |          |          |          |          |            |
| WP3 | Capillary blood collection                                        |          |          |          | X        |            | X          |          | X         |           | X           |           | X        |          | X        |          |          |            |
| WP4 | Data analysis and reporting                                       |          |          |          |          |            |            |          |           |           |             |           |          |          |          |          |          |            |

## 2.3 Operational definitions

|                |                                                                                                                                              |
|----------------|----------------------------------------------------------------------------------------------------------------------------------------------|
| Study center   | One of the partners involved in this study responsible for testing (, Catholic University of Leuven, Ghent University, University of Liege,) |
| CRC            | Clinical Research Coordinator (CRC), person assigned at each study center, responsible for data collection and follow-up of this study.      |
| Contact person | A local NH staff member, assigned as the contact person for communication between the study center and the NH for this specific study.       |

## 2.4 Study design and population

We plan to perform a longitudinal cohort study with a 2-month interval serial sampling of 3036, NH residents (1656) and staff (1380), spread over 69 nursing homes throughout Belgium. Sample collection at baseline (day 0, month 0) will start in a staggered way, so all samples among the different nursing homes are collected within the first  $\pm$  four weeks after collection of the first sample. Follow-up sample collection will occur with a 2-month interval in month 2, month 4, month 6, month 8, month 10 after the baseline collection of that specific nursing home. Ideally, in each NH, the 2nd, 3rd, 4th, 5th and 6th sample collection will take place d 60, 120, 180, 240 and 300 days after the first NH sample collection. However, when collection after 60 days is not possible for practical reasons, samples should be collected within a margin of  $\pm$  7 days.

The recruited NHs will be equally spread across the Belgian territory according to geographic and demographic characteristics to guarantee general representativity. Forty-four participants (20 staff, 24 residents) will be randomly included per nursing home.

### 2.4.1 Inclusion and exclusion criteria

NH residents and staff are considered for inclusion in the study. Both residents/staff that did experience COVID-19(-like) symptoms or had a positive COVID-19 test before, as well as residents/staff that did not experience COVID-19(-like) symptoms can participate in this study.

Participants can be included if they are  $\geq 18$  years old, have been informed (orally and by means of a written information form) on the goal of the study and the procedures of the study and have agreed to participate in the study by means of a signature on the informed consent form. In some cases, NH residents can give oral consent to their legal representative or caregiver, who will confirm this oral consent by their signature. Service flat residents are not considered as target population in this study and are therefore excluded. Temporary staff, employed for a period of less than 1 year starting from baseline collection, will also be excluded. Participants who are unable to provide a capillary blood sample for the point-of-care (POC) test will also be excluded.

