### *Stratified random sampling of participants*

Nursing homes that have agreed to participate will be asked to make an alphabetic list of the current staff/residents separately (service flat residents and temporary staff excluded) and to send the number of residents and staff to the Ghent University. Staff/residents will be sampled in a 5:6 ratio in each nursing home. Online statistical computing web programming will be used to generate the random sampling schedule out of the staff and resident numbers. The list of randomly selected numbers, including a list with substitute numbers, will be sent back to the NH. The NH's have to sample 20 staff and 24 residents out of their alphabetic list according to delivered random generated numbers.

When a participant refuses (after asking for oral consent) to join the study the subject according to the first following numeric list will be asked to participate. The participants will be assigned to a unique identification code of the following format: CX(X)SXXY or CX(X)RXXY for staff and residents respectively (C, nursing home (centre); S, staff; R, resident). In this way, test results and medical data are pseudonymized for the involved researchers. The link between the identification code and personal data will be safeguarded by the principal investigator. The oral consenting will be confirmed by a means of a signature before or on the day of the first data collection.

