#### **5.4 Informed consent**

Information on the study will be provided by the NH or the CRC/researcher sampling team and informed consent will be obtained from all participants, in their working language. The informed consent (Dutch and French) is attached in respectively Appendix 6.1 and 6.2.

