## 6. Appendices

### 6.3 Appendix 3: Questionnaires (Dutch/French)

#### VRAGENLIJSTEN BIJ AANVANG VAN DE STUDIE

##### Vragenlijst woonzorgcentrum (in te vullen bij aanvang studie)

1. Studiereferentienummer van het woonzorgcentrum
2. Hoe is de verdeling in zorgcategorieën van de bewoners van het woonzorgcentrum (in absolute aantallen)?  
O:    A:    B:    C:    Cd:    D:
3. Vond er reeds een COVID-vaccinatieronde plaats in het WZC?
  - a. 1ste ronde / 2de ronde (datum)
  - b. Welk vaccin?
    - i. AstraZeneca/Oxford vaccin
    - ii. Het BioNtech-Pfizer vaccin
    - iii. Het Moderna vaccin
    - iv. Andere
2. Hoeveel bewoners werden gevaccineerd (in verhouding tot het totale aantal bewoners?)
3. Hoeveel medewerkers werden gevaccineerd (in verhouding tot het totale aantal medewerkers?)
4. Werd uw WZC getroffen door één of meerdere COVID-19 uitbraken (= meerdere besmettingen in dezelfde periode die – vermoedelijk - aan elkaar gelinkt kunnen worden) vanaf het begin van de crisis tot nu?
  - a. In welke periode /perioden werd het WZC getroffen?
  - b. Hoeveel personeelsleden en bewoners (bij benadering) werden toen in dezelfde periode positief getest?
5. Hoeveel vermoede of bevestigde COVID-19 besmettingen zijn er binnen het WZC geweest bij bewoners vanaf het begin van de crisis tot nu (bij benadering) (incl. overleden bewoners)?
6. Hoeveel vermoede of bevestigde COVID-19 besmettingen zijn er binnen het WZC geweest bij medewerkers vanaf het begin van de crisis tot nu (bij benadering)
7. Hoeveel bewoners zijn aan COVID-19 overleden vanaf begin crisis tot nu (bij benadering)?
  - a. Bevestigde COVID-19 overlijdens
  - b. Vermoedelijke COVID-19 overlijdens
8. Hoeveel bewoners zijn aan niet-COVID gerelateerde oorzaken overleden vanaf het begin van de crisis tot nu (bij benadering)

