**Versie voor deelnemende bewoners**

*(in te vullen door de onderzoeker; bevragen bij de (hoofd)verpleegkundige of de vertegenwoordiger van de bewoner)*

Beste bewoner, beste vertegenwoordiger van de bewoner

1. Gelieve het uniek studienummer van de deelnemer in te vullen. (cfr lijst met random cijfers en studienummers, terug gestuurd door het onderzoekscentrum UGent)
2. Gelieve de leeftijd van de deelnemer in te vullen.
3. Wat is het geslacht van de deelnemer? M/V
4. Tot welke zorgcategorie behoort de bewoner?  
O:    A:    B:    Cc:    Cd:    D:
5. Verblijft de deelnemer in een afdeling voor bewoners met dementie?
6. Lijdt de deelnemer aan 1 van volgende aandoeningen? Duid aan wat van toepassing is (meerdere antwoordmogelijkheden).
  - Hart- en vaatziekten
  - Diabetes
  - Hoge bloeddruk (hypertensie)
  - Ernstige long-/hart-/nierziekte
  - Verzwakt immuunsysteem (immunosuppressieve aandoeningen) of immuunsysteem verzwakt door langdurig gebruik van immunosuppressieve medicatie (vb. chemotherapie, transplantatiepatiënten, immunosuppressieve reumamedicatie,...)
  - Actieve kankeraandoening
  - Geen van bovenstaande
7. Is de deelnemer gevaccineerd tegen COVID-19?
  - Ja, 1 dosis
  - Ja, 2 dosissen
  - Neen
    - Zo ja, welk vaccin kreeg de deelnemer toegediend
      - Het AstraZeneca/Oxford vaccin
      - Het BioNtech-Pfizer vaccin
      - Het Moderna vaccin
    - Zo ja, datum van vaccinatie (eerste spuit).
- 8.
9. Is de deelnemer ooit getest geweest op het coronavirus (via PCR/ag-sneltest/of radiologisch via CT-scan)? Ja/Nee
10. Zo, ja. Is de deelnemer ooit positief getest geweest op het coronavirus?
  - Ja, via PCR-test (test waarbij men via een neuswisser een staal afneemt en u na labo-analyse het resultaat krijgt)
  - Ja, via antigeen sneltest (test waarbij men via neuswisser een staal afneemt en men binnen het kwartier het resultaat kan aflezen)
  - Ja, radiologisch, via een CT-scan

- Neen

11. Zo ja, datum van 1ste positieve PCR-test of sneltest (bij benadering)?

12. Indien COVID-19 radiologisch bevestigd werd via een CT-scan , vermeld de datum van deze CT-scan.

13. Heeft de deelnemer tussen februari 2020 en nu een periode 1 of meerdere van volgende symptomen ervaren, zonder dat hier een duidelijke verklaring voor was? Duid aan wat van toepassing is (meerdere antwoordmogelijkheden).

- Hoest
- Kortademigheid
- Pijn op de borst
- Smaakverlies
- Geurverlies

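### As written, residents enter only on their own agreement, so the resident estimates may not cover all nursing home residents; care-category data already collected could correct part of this

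*Protocol*

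**What the plan says.** **Consent.** Section 2.4.1 requires that participants "have agreed to participate in the study by means of a signature on the informed consent form". For residents it adds: "In some cases, NH residents can give oral consent to their legal representative or caregiver, who will confirm this oral consent by their signature". In that second route the other person confirms what the resident has said and does not decide in the resident's place. Section 5.4 states that "informed consent will be obtained from all participants, in their working language". The consent forms themselves (Appendices 6.1 and 6.2) are not in the text at hand.

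**Sampling.** Section 2.6 has each home draw from an "alphabetic list of the current staff/residents separately (service flat residents and temporary staff excluded". Residents who cannot agree are therefore on the list. Section 2.4 fixes 24 residents per home. The substitution rule in section 2.6 reads: "When a participant refuses (after asking for oral consent) to join the study the subject according to the first following numeric list will be asked". Section 2.6 has reasons for refusal documented for homes, to assess selection bias; no matching record is stated for residents who are passed over.

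**Data on care category.** The baseline home questionnaire in Appendix 6.3 asks for the number of residents in each care category: "Hoe is de verdeling in zorgcategorieën van de bewoners van het woonzorgcentrum (in absolute aantallen". The baseline resident questionnaire records each participant's own care category and asks whether the participant lives on a dementia ward: "Verblijft de deelnemer in een afdeling voor bewoners met dementie".

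**Analysis.** The primary objectives in section 2.1 concern nursing home residents and staff in Belgium. Section 3.2 estimates seroprevalence by GEE and sero-incidence by clustered Poisson or binomial regression, without care category in either. Care profile appears only as a possible adjuster in the model for death among vaccinated residents. Section 4.3 does not list selection by ability to consent among the limitations.

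**The concern.** The population named in the objective is wider than the population that the consent rule can reach. Residents are drawn at random from a list that includes those who cannot agree, but only those who can agree may be enrolled, and the number per home is fixed. If ability to agree is related to antibody status, the resident seroprevalence and sero-incidence, and the totals that include them, are shifted by an amount that a larger sample does not reduce and that the confidence interval does not show.

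The protocol already has the means to examine part of this. It collects the same characteristic, care category, for the whole home and for each sampled resident, and then does not use it in the primary estimates.

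**Working it through.** **1. The plan's own precision figures (section 2.5).** At p = 0.5 the Wilson half-width is z / (2 × √(n + z²)), with z = 1.96.
- n = 381: 1.96 / (2 × √384.84) = 0.04996, the smallest n that meets 5 points.
- Sero-incidence: 381 × (1 + 0.12 × 14) = 381 × 2.68, rounded up to 1022; 1022 / 15 gives 69 homes and 1035 participants.
- Seroprevalence: 381 × (1 + 0.12 × 43) = 381 × 6.16, rounded up to 2347; 2347 / 44 gives 54 homes and 2376 participants.
- 69 × 44 = 3036 (1656 residents, 1380 staff).

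All of these reproduce. The point disputes no stated figure.

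**2. Precision for residents alone.** The planned 5 points are for residents and staff together, so a resident figure is needed for comparison.
- Design effect: 1 + 0.12 × (24 - 1) = 3.76
- Effective n: 1656 / 3.76 = 440.4
- Half-width at p = 0.5: 1.96 / (2 × √(440.4 + 3.84)) = 0.0465, about 4.6 points

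This uses the protocol's ICC of 0.12, which it states for residents and staff together.

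**3. Bias from selection.** Let f be the share of residents who cannot agree and d the absolute difference in seroprevalence between those who can and those who cannot. True prevalence = (1 - f) × P(can) + f × P(cannot), so the estimate from those who can agree is off by f × d. The documents give neither f nor d; both ranges below are assumptions.

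| f | d = 5 points | d = 10 points | d = 15 points |
|---|---|---|---|
| 10% | 0.5 | 1.0 | 1.5 |
| 20% | 1.0 | 2.0 | 3.0 |
| 30% | 1.5 | 3.0 | 4.5 |
| 40% | 2.0 | 4.0 | 6.0 |

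**4. Effect on the interval.** With a standard error of 4.65 / 1.96 = 2.37 points and a normal approximation, coverage of the nominal 95% resident interval is about 94.5% at a bias of 0.5 points, 76% at 3.0 points and 28% at 6.0 points.

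**5. Effect on the total.** Residents are 24 of 44 participants. If staff are unaffected, the bias in the total is 0.5 × 24/44 = 0.27 to 6 × 24/44 = 3.27 points, that is, about 0.3 to 3.3 points.

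**6. Whether the forms support a correction.** The Dutch home form lists categories O, A, B, C, Cd and D; the Dutch resident form lists O, A, B, Cc, Cd and D. The French forms show the same mismatch of C and Cc. The two sets can be used together once C and Cc are aligned.

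**The case against.** Several points on the other side are sound.

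- **The consent appendices are not shown.** A route on the representative's decision could stand there. What can be said is that section 2.4.1 does not give one; if the appendices do, they and section 2.4.1 need reconciling.
- **Replacement is inferred.** A reader might infer that the protocol orders residents who cannot agree to be replaced by the next number. It does not: section 2.6 words substitution for refusal. Replacement follows from the consent criterion, the fixed quota and the existence of a substitute list, and is likely rather than stated.
- **Residents with dementia are not barred.** The dementia-ward item, and the questionnaire answered by a nurse or representative, show that some are expected. The selection is by ability to agree, not by diagnosis or dependence.
- **Representativity.** A reader might take section 2.4's wording on representativity as a promise about residents that is then broken. That sentence concerns how homes are spread by geography and demography. The mismatch is with the population named in section 2.1 only.
- **The harm is not shown.** Nothing in the protocol says how antibody status differs between residents who can and cannot agree. The range spans a factor of twelve, starts at a negligible value and has no sign.
- **Consent and the SAP.** Every consent-based survey has some such selection, and weighting is often left to the SAP. But section 3.2 states the primary method, and the target population and limitations belong in the protocol.
- **Care category is a partial proxy.** A reader might infer that the collected counts repair the bias. They correct only what care category explains, and the documents do not show how closely it follows ability to agree.
- **Sero-incidence needs care.** Those at risk are sero-negative residents, while the home counts cover all residents. Standardising incidence directly to those counts would target the wrong group.

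**Conclusion.** The point holds in a limited form. On the visible text, enrolment depends on the resident's own agreement, the sampling list does not, and the primary estimates are for nursing home residents in Belgium without any use of care category. The resident estimates may therefore describe residents able to agree rather than all residents.

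Neither the existence, the direction nor the size of a bias can be established from the protocol. Under the assumed 10-40% excluded and 5-15 point difference, it would lie between negligible and somewhat more than the resident-only half-width; in the total it would be a little over half as large, provided staff are unaffected. The documents do not support saying that the estimates are biased by a given amount, or that weighting would remove the problem. The finding supports a cheap improvement to the analysis and a plain statement of scope.

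**What to change.** 1. **Section 3.2, seroprevalence.** Add a resident seroprevalence post-stratified to the care-category distribution reported by the homes, and report it beside the unweighted estimate. Post-stratify over all homes or by region, not within a home, where 24 residents are too few. Align C with Cc first, and pool sparse categories.
2. **Section 3.2, sero-incidence.** Build the weights on all sampled residents at baseline, and only then restrict to the sero-negative residents at risk.
3. **Sections 2.1 and 4.3.** State that the results cover residents able to agree to take part, and that weighting removes only the selection explained by care category.

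The cost is analysis and protocol wording: both data items are already on the baseline forms. The downside is slightly wider intervals for the weighted estimates. Consent procedures are unchanged.
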